#### Drop-out analyses

We define as “drop-out” any participant who did not complete the post-treatment measurement. Systematic differences in dropout rates between the three groups will be analyzed by a Fisher exact test. In addition, differences between participants and drop-outs in terms of sociodemographic and clinical variables will be considered.

#### Interim analysis

In case of a rejection of the licensing process by the inspecting federal institute for drugs and medical devices, an interim analysis of the treatment effect of the APP condition on outcomes of the main study (LSAS, WHO-QOL-BREF, PDI) could turn out to be necessary. Such interim analysis will be blinded, that is, performed by different researchers than the respective research teams of the study and after reaching a sample size of *n* = 30 for the APP and for the WLC group at post-treatment (based on a one-tailed power analysis simulation in R for a mean difference between two independent groups with unequal variance and effect size of *d* = 0.35, a standard deviation of outcome variables of 0.7 for both groups and 80% power). To account for multiple hypothesis testing, the alpha error level will be adjusted according to Pocock [65]. The interim analysis will not affect the continuation of the study.

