We based our power analysis on an iterative simulation of increasing sample sizes with starting values of *n* = 30 for the control condition and *n* = 50 for each of the treatment conditions, increasing stepwise by one participant per condition. The variance of the random intercepts and residual variance was set to 0.5 respectively [24]. Because missing values due to the dropout of participants were planned to be imputed by the jump to reference method (J2R) [25], the reference being the control condition, we reduced our expected effected sizes by multiplying them with the term (1—dropout-rate). Given a dropout rate of 26% at post-treatment evaluation in the study by Stolz et al. [16] and a pooled post-treatment dropout rate of 26.2% in a meta-analysis of studies using smartphone apps by Torous et al. [26], we chose a conservative estimate of 30% post-treatment dropout for the APP condition and multiplied the expected effect size of 0.5 by 0.7, equaling to *d* = 0.35. For the TG-APP condition, we expected a lower post-treatment dropout rate of 20% due to the additional guidance by a therapist and multiplied the expected effect size of 0.8 by 0.8, equaling to *d* = 0.64. Based on 500 simulations of the linear mixed model fitted with the expected effect sizes, we obtained the power of finding a statistically significant interaction of group × time based on a likelihood ratio test, compared to finding only main effects, and the 95% confidence interval for this estimate, for increasing sample sizes. We located the minimum sample size in our results after which the lower bound of the 95% confidence interval did not fall below 80% power, given *α* = 0.05. This condition was met at *n* = 41 for the control group and *n* = 61 for both treatment conditions (power estimate = 84%, 95% confidence interval = 80.0, 87.0). In addition to our study purposes, the app provider intends to use the results of the pilot study and the main study for the licensing process of the app as a digital health product. For this licensing process, a separate statistical analysis will be conducted comparing only the APP condition with the WLC condition, using a *t*-test for statistical analysis. A corresponding additional sample size calculation revealed the need to recruit 43 subjects in the wait-list control group (WLC). To establish conformity across the planned analyses we adjusted the number of participants for WLC upward to *n* = 43, resulting in a total sample size of *N* =165 (see also Fig. 1).

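### The stated inputs for the interim APP vs WLC analysis at n = 30 per arm do not give 80% power: they give about 61% or 38%, depending on how d = 0.35 is read, before any Pocock adjustment.

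*Protocol article*

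**What the plan says.** The Interim analysis section of the protocol article allows for an interim look at the APP effect on LSAS, WHO-QOL-BREF and PDI, should the licensing application be rejected. It would take place "after reaching a sample size of *n* = 30 for the APP and for the WLC group at post-treatment". That number is attributed to a "one-tailed power analysis simulation in R for a mean difference between two independent groups with unequal variance", an "effect size of *d* = 0.35", and "a standard deviation of outcome variables of 0.7 for both groups and 80% power". No numerical alpha appears in the section. On multiplicity it says: "To account for multiple hypothesis testing, the alpha error level will be adjusted according to Pocock". It gives neither a nominal level nor a number of looks. It adds that the result will not change whether the study continues.

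The value 0.35 comes from Design and sample size, where the expected APP effect was reduced for 30% dropout: "multiplied the expected effect size of 0.5 by 0.7, equaling to *d* = 0.35". That section sizes the main trial with the criterion that the lower confidence limit "did not fall below 80% power, given *α* = 0.05".

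**The concern.** The interim section gives n, effect, SD, sidedness and power together, so with a value for alpha the power can be checked directly. A quick check suggests a large gap: 30 per arm is small for a standardised effect of 0.5, and much too small for 0.35.

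The interim serves only to support the app in the licensing process after a rejection. If its power is really nearer one half than four fifths, the team and the licensing body would expect more from it than it can deliver, and a non-significant result could be taken as stronger evidence against the app than it is.

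A smaller point concerns the same sentence. It specifies unequal variances but gives one SD for both groups, so the simulation that was run cannot be identified from the text.

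**Working it through.** **Inputs**
- n = 30 in APP and 30 in WLC, one-tailed, two independent means, 0.35, SD 0.7, power 80%: Interim analysis.
- Alpha: not stated there. One-sided 0.05 is assumed, because 0.05 is the level used in Design and sample size.
- Pocock level: not stated. Two looks, the first at half the information, and an overall one-sided 0.05 are assumed. Solving P(Z1 > c or Z2 > c) = 0.05 with correlation √0.5 gives c = 1.875, a nominal one-sided level of 0.0304.

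**Formula**

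With standardised effect δ and n per arm, the noncentrality is δ·√(n/2). Power is the probability that a noncentral t with 2n − 2 = 58 degrees of freedom exceeds the critical value. For n = 30, √(n/2) = √15 = 3.873. The critical value is 1.672 at 0.05 and 1.913 at 0.0304.

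**Attempt to reproduce 80%**

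| Reading of 0.35 | δ | Noncentrality | Power at 0.05 | Power at 0.0304 |
|---|---|---|---|---|
| Raw difference, SD 0.7 | 0.35/0.7 = 0.50 | 0.50 × 3.873 = 1.936 | 60.6% | 51.3% |
| Already standardised | 0.35 | 0.35 × 3.873 = 1.356 | 38.0% | 29.4% |

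The normal approximation agrees at 0.05: Φ(1.936 − 1.645) = 61.5% and Φ(1.356 − 1.645) = 38.6%. A Welch t-test simulation with 200,000 replicates, which allows for unequal variances, gives 60.6% and 37.9%.

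**Other readings of the sentence at n = 30**
- Two-sided 0.05: 48% or 26%.
- One-sided 0.10: 74% or 53%.
- 0.7 taken as a variance (δ = 0.35/√0.7), one-sided 0.05: 48%.
- Baseline adjustment with an assumed correlation of 0.5, one-sided 0.05: 71% or 46%.

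None of these reaches 80%.

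**What 80% would need**
- At 30 per arm and one-sided 0.05: δ of about 0.65.
- With equal arms at one-sided 0.05: 51 per arm for δ = 0.50, or 102 for δ = 0.35.
- With equal arms at 0.0304: about 60 or 122 per arm.

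**Inputs that would come close**

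With the undiluted effect as a raw difference, δ = 0.5/0.7 = 0.714 and the noncentrality is 0.714 × 3.873 = 2.766. Power is then 86% at 0.05 and 80.2% at 0.0304. This matches n = 30 and 80%, but it is not what the section prints.

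**The case against.** The best defence is that only the printed effect size is a slip. The 30 per arm are counted at post-treatment and can be read as completers, for whom the dropout reduction from 0.5 to 0.35 would not apply. A difference of 0.5 with SD 0.7 then gives 80.2% at the assumed Pocock level. This is plausible but is an inference. It does not rescue the sentence, which states 0.35. It does bear on the remedy: inserting 61% without checking the simulation could fix the wrong number in the protocol.

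It is also fair that one-sided 0.05 is an assumption. A stricter level widens the gap, and even one-sided 0.10 gives at most 74%.

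A reader might infer several stronger points that the document does not support:
- **The interim will probably fail even if the app works as assumed.** On the raw-difference reading, power is 61%, or 51% after Pocock. Only the standardised reading makes failure the likelier result.
- **The trial cannot reach 80% for this comparison, because 51 per arm exceeds the 43 planned in WLC.** The figure of 51 assumes equal arms. The planned 61 APP and 43 WLC give 80.2% at δ = 0.50, one-sided 0.05.
- **The interim lowers the power of the main three-group test.** The article describes the licensing comparison as a separate APP vs WLC analysis and nowhere carries the Pocock level to the group × time test.
- **n = 30 means the whole WLC arm after 30% dropout.** The article gives dropout rates for APP and TG-APP but none for WLC.
- **SD 0.7 contradicts the main power analysis.** There, "The variance of the random intercepts and residual variance was set to 0.5 respectively". Those are components of a mixed model for LSAS; the interim SD refers to several outcome variables, and 0.7 is close to √0.5. The choice is unexplained, but a conflict is not shown.
- **The Pocock level and the ranking of the three outcomes are missing.** Such details are commonly left to an analysis plan, which is not at hand.

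**Conclusion.** The point stands as an internal numerical error. The power stated for 30 per arm does not follow from the effect, SD and sidedness stated with it. At an assumed one-sided 0.05 the shortfall is about 19 percentage points (80 − 61) if 0.35 is a raw difference, and about 42 (80 − 38) if it is standardised. At an assumed two-look Pocock level of about 0.030, power is about 51% or 29%. The document does not settle which input is at fault.

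The reach is limited. The interim happens only if licensing is rejected, does not affect continuation, and concerns APP vs WLC alone. The primary analysis and N = 165 do not rest on it. The sentence should be corrected, but the error does not threaten the validity of the trial.

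**What to change.** In the Interim analysis section:
1. Rerun the simulation and report the inputs actually used. Say whether 0.35 or the undiluted 0.5 applies, and whether it is a raw difference or a standardised effect.
2. Give one coherent variance assumption: either a different SD for each group, or a common SD without the reference to unequal variances.
3. State alpha and its sidedness, and replace the 80% with the power that the reconciled inputs deliver at n = 30 at the Pocock-adjusted level. Alternatively, change n to fit.
4. If 0.35 as a raw difference and SD 0.7 stand, state about 61% before and about 51% after Pocock, on the alpha and two-look assumptions used here.

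The cost is a short simulation and a few words of protocol text. The only downside is that the stated power may become less favourable.

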## Discussion

Based on a recent meta-analysis, there is evidence that internet- or app-based interventions have moderate effect sizes in the treatment of SAD [12]. There is also preliminary evidence from previous studies that internet-based cognitive behavioral therapies (ICBTs), based on the model of Clark and Wells [4], may achieve large effect sizes [15, 16, 66]. These findings are consistent with results demonstrating the superiority of CBT based on Clark and Wells’ model in regular face-to-face therapy [5]. In our study, we plan to extend these findings by conducting an RCT comparing the efficacy of a mobile app based on Clark and Wells’ model with the efficacy of the app plus additional therapist-guided sessions delivered via video and a wait-list control group.

We hypothesize that the addition of therapist-guided sessions will result in larger effect sizes than using the app alone. In agreement with Stott et al. [15], we assume that contact with a therapist has a critical impact on engagement in specific CT interventions, particularly behavioral experiments. Similar to exposure-based treatments, the presence of a therapist assists the patient in overcoming avoidance, shifting attention outward, and identifying and discontinuing safety behaviors and ensures that feared negative evaluation is challenged. Therefore, therapist-guided sessions can prevent the underuse of behavioral experimentation, an important effective component of CT according to Clark and Wells’ model.

To summarize, our results will demonstrate (a) the efficacy of a new app-based intervention using the Clark and Wells approach in another well-designed and preregistered independent trial and (b) whether additional face-to-face therapy is beneficial to patients in terms of increased symptom reduction of SAD compared to app use alone. The results will be critical for service delivery and treatment planning for social anxiety disorder.

### Organizational structure

#### Coordinating center and trial steering committee

The present study is a bicentric study which is designed and coordinated in a cooperation between the Goethe University Frankfurt and the Technische Universitaet Dresden. The study team has weekly meetings. There is no additional steering committee.

Support for the trial is provided by:Principal investigator: provides supervision for the treatment, has medical responsibility of the patients, designs and plans the studyStudy coordinator: coordinates study procedures, responsible for administrative tasks, reviews study progressStudy therapists: responsible for the implementation of the therapiesClinical raters: responsible for conducting independent clinical evaluations with respect to outcome criteria and inclusion and exclusion criteria

#### Data monitoring committee

There is no data monitoring committee and no independent auditing process. The quality of the data is assured by the blinded clinical raters and there are no known serious adverse effects. If serious adverse effects occur, they will be reported to the principal investigator, who will then interview the patient in question and refer them to a psychiatry if needed. Adherence to therapeutic measures is ensured by regular supervision by the principal investigators. Completeness of data will be regularly verified by the study coordinators.

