**Methods/design:**

A within-between interaction design with randomization to one of three conditions will be used. In the APP condition, patients receive only the app without any additional contact with therapists, while in the TG-APP condition, therapists provide 8 sessions of video-based treatment in addition to using the app. The study will be conducted in two university outpatient treatment centers with reliably diagnosed SAD patients. The primary outcome will be defined as change in SAD symptoms, as measured by the Liebowitz Social Anxiety Scale (expert rating). Furthermore, a wide range of self-reports and clinician ratings for other symptoms (depression, general psychopathology) or quality of life will be used. A simulation-based power analysis for a 3 × 2 interaction effect (group × time) on the primary outcome in a linear mixed model resulted in a total sample size of *N* = 165.

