Previous studies that have examined the effectiveness of ICBTs have largely used treatment programs delivered via a computer. Today, however, the use of a smartphone including its apps is even more widespread, rendering mobiles a promising option for the treatment of mental disorders. It might even have more advantages than ICBTs delivered via a computer, as apps seem to be easily integrated into daily routines [16] and are convenient for both the patient and the practitioner [17]. Furthermore, using a mobile phone has the advantage that patients can use protocols or other forms of assessments when the situation occurs so that some forms of perception and reporting biases can be minimized [18]. As an example, Stolz et al. [16] have been able to show that an app based on the Clark and Wells [4] treatment approach with text-based guidance during the process can significantly reduce symptoms of social anxiety. However, it remains unclear whether their app would also work without additional guidance.

This raises the important research question of whether the effectiveness of apps can be enhanced by accompanying face-to-face sessions with a therapist. To date, few studies have addressed this question. The authors assume that therapist guidance could additionally increase compliance with ICBT treatment as well as the motivation to complete it. Another advantage of therapist-guided ICBT over nonguided ICBT could be higher patient safety, as the therapist can assist when questions or ambiguities arise, or when adverse side effects of ICBT occur, such as worsening of symptoms, negative well-being, or noncompliance [19].

Particularly as a result of the COVID-19 pandemic, new ways of providing therapeutic support have been developed: Due to the limitations of physical contact, the use of videoconferencing has increased dramatically. A meta-analysis has shown that video-based psychotherapy typically has large effect sizes and that the difference to in-person therapy is negligible [20]. The use of this modality to treat mental disorders could be an important step in increasing accessibility to psychotherapy, not only because of the ongoing (or possibly recurring) pandemic situation, but also to overcome other barriers to in-person treatment, such as illnesses that limit the scope of activities, specialized treatment programs that exist only in distant locations, or difficulty finding a therapist in rural areas.

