### Procedure

The study will be conducted in Germany at the outpatient psychotherapy unit of the Clinical Psychology department of the Goethe University of Frankfurt as well as the outpatient psychotherapy unit of the Clinical Psychology department of the Technische Universitaet Dresden and two further CBT training centers in Dresden. For reporting purposes, we followed the SPIRIT reporting guidelines [27].

In the first step, all persons that register for participating in the study will be screened using an online self-report assessment. If participants exceed the cut-off of 25-points or find themselves within the criteria for social anxiety disorder, they are referred to another online self-assessment and then invited for an interview with a clinical rater. Beforehand, they will be informed about the study and provided with written informed consent (either personally or via email if necessary). Interviews to determine the patient's formal diagnosis are conducted by blinded and independent psychologists (with at least a master’s degree) who have been trained in the appropriate interviews. Eligible patients are then randomly assigned to one of three groups (WLC, APP, TG-APP). Participation in each of the groups lasts 3 months. Participants in the WLC group then have the option of using the app if they wish. The outcome measures will be assessed by blinded and independent raters at baseline, post-treatment (3 months after start), as well as 6 months after the post-treatment interview (follow-up). Furthermore, participants will complete self-report questionnaires online at baseline, at mid-treatment (at 6 weeks), post-treatment (at 12 weeks), and follow-up (at 36 weeks; see Fig. 1 for the study flowchart). Interviewers will remind patients to fill out the self-report questionnaires and if necessary, patients will be contacted by the study coordinator to complete the missing questionnaires.

Prior to the start of the study, we will conduct a pilot study to improve usability and evaluate the mobile application and the applicability of therapist-guided video therapy and the videoconferencing tool.

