### Ethical issues

The study was approved by the Ethics Committee of the Department of Psychology at Goethe University Frankfurt. If post-trial care is required (e.g., in case of serious adverse effects), this will be provided by the outpatient clinics in Frankfurt and Dresden, and participants will be referred to a hospital or psychiatric clinic if necessary.

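### Serious events reach the principal investigator only by passive report, and only TG-APP has scheduled therapist contact before week 12, so any by-arm listing is open to unequal ascertainment

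*Protocol article*

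**What the plan says.** The section on the data monitoring committee states that there is no such committee and that "there are no known serious adverse effects". It then gives the one rule for serious events: "If serious adverse effects occur, they will be reported to the principal investigator, who will then interview the patient in question", with onward referral if needed. The section on ethical issues adds: "If post-trial care is required (e.g., in case of serious adverse effects), this will be provided by the outpatient clinics".

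Contact with therapists differs by arm. The abstract says "In the APP condition, patients receive only the app without any additional contact with therapists", whereas in TG-APP "therapists provide 8 sessions of video-based treatment in addition to using the app". No therapist contact is described for WLC before week 12.

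Other contacts are described without exempting any arm. Under Procedure, "The outcome measures will be assessed by blinded and independent raters at baseline, post-treatment (3 months after start", and again at follow-up. Also, "participants will complete self-report questionnaires online at baseline, at mid-treatment (at 6 weeks), post-treatment (at 12 weeks), and follow-up (at 36 weeks". Interviewers remind patients about questionnaires, and the study coordinator may contact those with missing forms. Both app arms, but not WLC, also complete the modified SPWSS weekly (Self-rating scales).

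Harms in general are collected on a seven-item self-report side-effect scale that contains an open item (Self-rating scales). That scale is the adverse-effect analysis named under Secondary analyses.

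**The concern.** When events are recorded only if someone happens to report them, the number recorded depends on how often a patient speaks to a person who would pass the news on. Here that opportunity is tied to the randomized arm. A TG-APP patient admitted to hospital in week 5 would probably mention it at the next video session. An APP or WLC patient with the same admission has no scheduled conversation with a clinician until the post-treatment interview, and even that is not stated to ask.

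The onward channel is unequal too. The principal investigator supervises treatment (Organizational structure), so a TG-APP therapist has a standing line to the person who must be told. No counterpart is described for the other two arms.

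The article itself accepts that therapists become aware of harms. In the Introduction it offers as an advantage of guidance that "the therapist can assist when questions or ambiguities arise, or when adverse side effects of ICBT occur". If serious events were later listed by arm, closer observation could make the guided arm look less safe, the opposite of what the authors expect. Serious events in a trial of this size would probably be few, so a handful missed in one arm could change the picture, and they cannot be recovered reliably afterwards.

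**Working it through.** The plan states no serious-event figure, so there is nothing to reproduce. The check has three parts.

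**1. Scheduled contact by arm, baseline to week 12.** Arm sizes are from Allocation and randomization (WLC 43, APP 61, TG-APP 61; 43 + 61 + 61 = 165).

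- TG-APP: 8 sessions in 12 weeks, 12 / 8 = one per 1.5 weeks on average.
- APP and WLC: no scheduled clinician contact between the baseline interview and the post-treatment interview. That is 61 + 43 = 104 patients, and 104 / 165 = 63%.

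**2. Do the common contacts fill the gap?** The week-6 and week-12 questionnaires, the interviews and the coordinator's follow-up of missing forms reach all arms, but none is stated to ask about serious events. The SPWSS rates anxiety, avoidance, attention, worry, rumination and approach behavior, with added items on pleasure and personal goals. The side-effect scale rates agreement with expert-chosen negative effects. Its open item could catch a serious event, but is not described as asking for one.

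Dropout thins the common week-12 assessment unequally. Under the planning assumptions in Design and sample size, 0.30 × 61 = about 18 APP patients and 0.20 × 61 = about 12 TG-APP patients would lack the post-treatment measurement, which is how Drop-out analyses defines dropout.

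**3. What unequal detection could do.** This is an illustration only: the risks and detection shares are assumptions, since the documents give none. Let the true risk be the same in every arm.

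- Expected recorded events = n × risk × share detected.
- Chance of recording none = (1 − risk × share)^n.

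With risk 5% and 90% detected in TG-APP, TG-APP expects 61 × 0.05 × 0.9 = 2.745 events, with a 6% chance of recording none. For the other arms:

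| Share detected in APP and WLC | APP expected | WLC expected | APP, chance of none | TG-APP:APP ratio |
|---|---|---|---|---|
| 90% | 2.745 | 1.935 | 6% | 0.9/0.9 = 1.00 |
| 70% | 2.135 | 1.505 | 11% | 0.9/0.7 = 1.29 |
| 50% | 1.525 | 1.075 | 21% | 0.9/0.5 = 1.80 |

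Over risks of 2% to 10%, TG-APP expects 1.1 to 5.5 recorded events; at 50% detection APP expects 0.6 to 3.1. The ratio does not depend on the risk, and it is 1.00 if detection is equal. WLC counts are also lower because the arm is smaller, so they should be read per patient.

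**The case against.** The strongest reply is that the rule is a patient-care step (report, interview, refer) and not a counting rule. The article plans no between-arm comparison of serious events. Its planned harms analysis uses a self-report scale that does not depend on therapist contact. Which arms complete that scale, and when, would be in the schedule figure, which is not shown, so unequal collection of scale data cannot be asserted. All of this stands, and it limits the point to any by-arm listing of serious events.

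It can also be said that a condensed article may leave definitions, reporters and event forms to the full protocol. That stands as well: their absence is not the complaint. What remains is that the route described is passive and sits on a contact schedule that differs by arm.

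Nor is it true that APP and WLC patients go unseen. They have a week-6 questionnaire and possible coordinator contact, and APP has weekly ratings. These are real contacts and are the natural place for the remedy, although none is stated to ask about serious events.

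Three stronger readings are tempting and not supported.

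- A reader might infer from the word *effects* that an event counts only once attributed to the intervention, so that a WLC event could never count. The text states no causality filter, and the Introduction uses similar wording loosely enough to include noncompliance.
- A reader might infer that APP will look cleanest in the licensing comparison. That comparison is APP against WLC, and WLC has no more contact than APP. The outcomes named for the possible licensing-related interim analysis are LSAS, WHO-QOL-BREF and PDI.
- A reader might see a contradiction between having no known serious effects and planning for them. A contingency plan is consistent with that statement, and deleting the statement would not change ascertainment.

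**Conclusion.** The point holds in a limited form. If the plan is followed as described, serious events arising before week 12 are more likely to come to light in TG-APP than in APP or WLC, so a by-arm listing could over-record TG-APP relative to the other two. The direction rests on two documented facts: the reporting is passive, and scheduled therapist contact exists in only one arm. It also assumes that patients tell therapists about such events and that no cause-neutral prompt exists elsewhere. The size is unknown, and the ratios of 1.00 to 1.80 above are illustrations, not estimates.

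A reader might go further and conclude that the trial's safety data as a whole cannot be compared across arms. The documents do not support that, because the planned side-effect scale analysis is not shown to be affected. The severity is minor: a cheap improvement to data collection, not the correction of an error in a planned analysis.

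**What to change.** 1. In the section on the data monitoring committee, word the rule as serious adverse events regardless of suspected cause. The described response to such an event need not change.
2. Add the same one or two closed items on serious events since the last assessment (for example, hospital or emergency care) to the existing online assessments at weeks 6, 12 and 36, in all three arms.
3. Put the same items in the coordinator's existing contact with non-responders. Otherwise the week-12 question will miss many of the patients who drop out.
4. Base any by-arm table of serious events on these common items only, and list separately those events learned only in therapy sessions.

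The cost is slightly longer forms and more events to list. No new visit or staff is needed.
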